### Intervention group

All intervention group participants receive treatment as usual, as described for the control group, and in addition receive WELLFOCUS PPT.

WELLFOCUS PPT is an 11-session intervention which aims to improve well-being in people with psychosis. All sessions begin and close with a music savouring exercise. Over the course of the 11 sessions, 10 exercises adapted from standard PPT are covered: positive introductions, savouring, good things, identifying personal strengths, personal strength activity, strength activity with significant other, forgiveness, one door closes another door opens, gratitude, and positive responding. All intervention exercises target at least one of the four target areas identified in the WELLFOCUS model. Every session develops an ‘ongoing exercise’, comprising an exercise to be completed, repeated, or reflected on in participants’ own time.

WELLFOCUS PPT is provided by two facilitators who follow the WELLFOCUS PPT manual (unpublished, on request from first author). Groups last approximately 90 minutes, with a 10 minute break in the middle. All facilitators have experience of facilitating therapeutic groups and of working with people with a diagnosis of psychosis. Facilitators are encouraged to show warmth, empathy, and genuineness in their interactions. Facilitators participate in all exercises themselves, they share personal examples from their own lives with the group, and are encouraged to do the ‘ongoing exercise’ in their own time. Participants are not prohibited from sharing distressing, unpleasant, or negative states and experiences in the group. Negative contributions are validated but not focused on. Instead, facilitators establish a link between the negative experience and one or more of the intervention’s target areas. Participants in the intervention group receive a phone call between each session to offer support with the ‘ongoing exercise’. All facilitators are invited to attend a monthly peer supervision meeting and we plan to report on the rate of attendance.

### Treatment fidelity strategies

We use principles for enhancing treatment fidelity outlined by the NIH Behavior Change Consortium [34], comprising strategies to increase treatment fidelity in five areas: study design, training providers, delivery of treatment, receipt of treatment, and enactment of treatment skills. Compliance with fidelity strategies will be assessed using checklists.

Fidelity strategies at the design level aim to ensure that a study can adequately test its hypothesis by ensuring the design is theory driven, and establishing procedures to standardise the dose and intensity, prevent contamination and deal with implementation setbacks. We used three fidelity strategies at study design level:

1. We use an evidence-based testable intervention model, i.e., the WELLFOCUS model.

2. To ensure the same treatment dose in all groups across the treatment arm, we send treatment reminders, work with fixed length group sessions, and a fixed number of mid-week telephone contacts per participant. We use a treatment manual which is followed in each group and provide the same information material to every participant.

3. To address possible implementation setbacks, we maintain a pool of trained facilitators, to avoid facilitator absence leading to group cancellations.

Fidelity strategies at the level of provider training aim to ensure adequate skill acquisition and skill maintenance of facilitators. We use three fidelity strategies at the level of provider training:

1. We provided two days of standardised training for all facilitators, led by the co-developer of standard PPT and the WELLFOCUS research team.

2. We provide monthly peer supervision sessions, which mirrors the group’s facilitator style and the focus on the four target areas as training boosters.

3. Following each session, both facilitators jointly write PPT-style notes on participants’ achievements in the four target areas, to avoid therapeutic drift.

Fidelity strategies at the level of treatment delivery aim to ensure provision of identical content across the individual groups in the intervention arm and to minimise contamination between arms. We use two fidelity strategies at treatment delivery level:

1. We manualised the intervention, using unpublished best practice guidelines (REMINDE – see http://www.equator-network.org/resource-centre/library-of-health-research-reporting/reporting-guidelines-under-development).

2. Facilitators met before each session to rehearse the session content as described in the manual, to minimise between-group differences.

Fidelity strategies at the level of treatment receipt aim to ensure that participants understand and perform the cognitive and behavioural skills delivered during treatment. This is an important and often neglected component of fidelity. If participants do not understand or are not able to implement the new skills during treatment, an otherwise effective intervention may be deemed ineffective. We use two fidelity strategies at the treatment receipt level:

1. To ensure participant comprehension we use concise and plain English information materials supported by pictures to avoid a focus on literacy.

2. The ‘ongoing exercise’ is supported and monitored by weekly calls and reviewed in the subsequent group session to increase both understanding and implementation of the involved skills.

Fidelity strategies at the level of treatment skills enactment aim to ensure that skills learned during the therapy are adequately applied in real-life settings. Enactment is different from treatment adherence and treatment efficacy. Treatment adherence relates to whether a participant performs a task definitive of a specific treatment (e.g., actually notes down a good thing that has happened) and treatment efficacy relates primarily to whether an intervention influences the hypothesised endpoint. Treatment enactment specifically relates to the extent to which a participant actually implements a new skill in their everyday life. It is possible that a study shows excellent enactment but poor adherence and poor efficacy. This would provide a good test of the intervention because the treatment skills are used but are not effective. By contrast, in a study with poor enactment neither adherence nor efficacy is likely to be high. We use two fidelity strategies at the level of skills enactment:

1. Participants are repeatedly reminded throughout the duration of the group of skills learned during past group sessions to encourage their ongoing application, e.g., savouring small things in everyday life or noticing good things and collecting them in a ‘good things’ box.

2. The last manualised session focuses on reflecting on the implementation of learned skills in everyday life.

### Measures

The primary outcome is the WEMWBS, a 14-item measure of positive well-being originally developed for the UK general population which frames well-being as a multi-dimensional construct [32]. The overall score is the sum of all items, varying from 14 (low well-being) to 70 (high well-being). The overall scale has proven feasible, reliable, and sensitive to change in people with various mental health problems, including psychosis [35]. Chronbach’s α for the scale lies between 0.87 and 0.91 and the one-week test-retest reliability at r = 0.83 [32,36].

Eight secondary outcomes are used.

#### Positive Psychotherapy Inventory (PPTI)

The PPTI consists of 25 questions rated on a 5-point Likert scale varying from “not at all like me” to “very much like me”. The overall score is the sum of all items, varying from 25 (low) to 125 (high). The scale contains five factors designed to assess the positive emotions, engagement, relationships, meaning, and accomplishment (each with a total score between 5 (low) and 25 (high)). It was specifically designed to capture changes due to PPT in clients [25]. The internal consistency of the scale was found at α = 0.80, its test-retest reliability at r = 0.81 in a sample of healthy participants [37].

#### Savouring Beliefs Inventory

The Savouring Beliefs Inventory is a 24-item scale that assesses individuals’ perceptions of their ability to derive pleasure through anticipating upcoming positive events, savouring positive moments in the present, and reminiscing about past positive experiences. It uses a 7-point Likert scale between “strongly disagree” and “strongly agree”. The overall score is computed by summing responses to the 12 positively-anchored items and subtracting responses to the 12 negatively-anchored items. Total scores can vary between −72 (low savouring beliefs) and +72 (high savouring beliefs) for the overall scale. Scores for the three subscales are calculated according to the same principle and can vary from −24 (low savouring beliefs on subscale) to +24 (high savouring beliefs on subscale). The overall scale showed an internal consistency of between α = 0.88 and 0.94 in different studies and a test-retest reliability of r = 0.84 [38]. It was also found feasible to use in people with psychosis [9].

#### Short Depression-Happiness Scale

The Short Depression-Happiness Scale measures affect on a bipolar continuum between depression and happiness [39]. It uses a 4-point Likert scale between “never” and “often”. The 6-item short version was found to have an internal consistency of between α = 0.77 and 0.92 in different studies, and a test-retest reliability of r = 0.68. The 3 positive items are reverse-scored which leads to overall scores varying from 6 (more depression) to 24 (more happiness). Preliminary normative data suggest that a score of 9 or less may be indicative of mild but clinically relevant depression [40].

#### Brief Psychiatric Rating Scale

The Brief Psychiatric Rating Scale is an 18-item observer-rated measure of psychiatric symptom severity [41]. It uses a 7-point Likert scale from “not present” to “extremely severe”. The overall score is the sum of all items, varying between 18 (low symptoms) and 126 (severe symptoms). The internal consistency of the overall scale lies between α = 0.65 and 0.79, its diagnostic sub-scales for withdrawal/retardation, thinking disorder, anxiety/depression, and activation vary from α = 0.766 to 0.879 [42,43]. Inter-rater reliabilities for this scale have been reported between 0.87 and 0.97. In terms of clinical interpretation, a total score of 31 was found to correspond to a clinical global impression rating of “mildly ill”, 41 to “moderately ill”, and 53 to “markedly ill” [44].

#### Integrative Hope Scale

The Integrative Hope Scale captures a comprehensive concept of hope and has been validated specifically for people with psychosis [45,46]. The scale contains 23 items that are rated on a 6-point Likert scale from “strongly agree” to “strongly disagree”. The 6 negatively anchored items are reverse-scored. The overall score is the sum of all items, varying between 23 (low hope) and 138 (high hope). The scale’s internal consistency lies at Cronbach’s α = 0.92 for the overall scale and the test-retest reliability at r = 0.84 in people with psychosis [45].

#### Rosenberg Self-Esteem Scale

The Rosenberg Self-Esteem Scale contains 10 items which are rated on a 4-point Likert scale from “strongly agree” to “strongly disagree”. The scale measures self-esteem by asking the respondents to reflect on their current feelings, with the 5 negatively anchored items being reverse-scored. The overall score is the sum of all items, varying between 0 (low self-esteem) and 30 (high self-esteem). Its psychometric properties have been repeatedly established in various client groups, including people with psychosis, and languages with the internal consistency found between α = 0.77 and 0.88, and the test-retest reliability between r = 0.82 and 0.88 [47,48].

#### Rogers Empowerment Scale

The Rogers Empowerment Scale is a 28-item instrument designed to measure subjective feelings of empowerment on a 4-point Likert scale varying from “strongly agree” to “strongly disagree”. After reverse-scoring of the 9 negatively framed items the sum of all items forms the overall score which can vary between 28 (low empowerment) and 112 (high empowerment). Its psychometric properties have been confirmed for people with psychiatric conditions, including psychosis, where the scale’s internal consistency was found at α = 0.86, and 6 of the 7 factors of the scale showed a re-test reliability of r >0.75 [49,50].

#### Sense of Coherence Scale

The Sense of Coherence Scale contains 29 questions to measure a person’s global orientation to view the world and the individual environment as comprehensible, manageable, and meaningful. It uses a 7-point scale Likert scale between “very often” and “very seldom or never”. Thirteen items are formulated negatively and have to be reversed for scoring. The overall score is the sum of all items, varying between 29 (low sense of coherence) and 203 (high sense of coherence). In different samples and translations, the scale showed an internal consistency of between α = 0.70 and 0.95, and a 1 year test-retest reliability from r = 0.69 to 0.78. [51].

In addition, five further measures are used. The Manchester Short Assessment of Quality of Life is an established 12-item measure that frames well-being in terms of subjective health-related quality of life and includes a specific item asking for satisfaction with life as a whole [52], which has been regarded as a measure of well-being in its own right [53]. The overall score is the mean of all item scores which can vary between 1 (low satisfaction with life) and 7 (high satisfaction with life). The scale’s internal consistence was found between α = 0.74 [52] and 0.81 [54] in different samples of people with mental illness. The Health of the Nation Outcome Scale is a widely used 12-item measure of social disability. Items cover a range of problem areas rated on a 5-point scale between 0 (no problem) and 4 (serious problem) with a resulting overall score of up to 48. Cronbach’s α for the scale varies between 0.59 and 0.76 [55]. The test-retest reliability was found to be mixed for all items, varying between r = 0.65 and 0.40 for seven items, and 0.31–0.32 for three items [56].

The Global Assessment of Functioning is an equally well accepted measure of functioning, which is used in a 2-item version assessing social and psychological functioning, each rated from 1 (most serious symptoms or disability) to 90 (no symptoms or disability) [57]. The items show an internal consistency of between α = 0.61 and 0.91, and a test-retest reliability of between r = 0.66 and 0.92 [58].

The CORE10 is a 10-item measure of symptoms. It is scored on a 5-point Likert scale from 1 “not at all” to 5 “most or all of the time” resulting in overall scores between 10 and 50. The scale’s internal consistency is α = 0.90 [59].

The Sociodemographics Form – Service User is a non-standardised measure modified from another RCT [60], which records the service user’s date of birth, gender, ethnicity, languages spoken, country of birth, education, employment, marital status, and housing. The rationale for inclusion of each outcome measure is shown in Table 1. Those in the intervention group additionally receive a process evaluation form at follow-up which asks to rate the effect of WELLFOCUS PPT on the hypothesised intervention model variables using a 10-point Likert scale.

**Table 1 T1:** Outcome measures used in the WELLFOCUS study

**WELLFOCUS model component**	**Measure**	**Rater**	**Rationale**
**Distal outcome**			
Personal well-being	WEMWBS	Patient	Measures overall well-being, i.e., enhanced sense of self
**Proximal outcomes**			
Good feelings	Savouring Beliefs Inventory	Patient	Assesses pleasure in the past present and future, which is a form of good feeling addressed in the intervention
	PPTI positive emotions	Patient	Assesses enjoyment and happiness, which is a form of good feeling addressed in the intervention
Symptom relief	Short Depression-Happiness Scale	Patient	Measures the reduction of depression, which is an intended outcome of PPT
	Brief Psychiatric Rating Scale	Researcher	Measures general symptom severity including psychosis-specific symptoms
	CORE10	Patient	Measures general symptom severity
Connectedness	PPTI relationships	Patient	Measures the presence of supportive relationships as a form of connectedness addressed in the intervention
Hope	Integrative Hope Scale	Patient	Measures hope, which is an indicator of well-being
Self-worth	Rosenberg Self-Esteem Scale	Patient	Measures self-worth, which is an indicator of well-being
Empowerment	Rogers Empowerment Scale	Patient	Measures empowerment, which is an indicator of well-being
Meaning	Sense of Coherence Scale	Patient	Measures meaning, which is an indicator of well-being
	PPTI meaning		Provides a PPT-specific measure of meaning
**Other outcomes**			
Quality of Life	Manchester Short Assessment of Quality of Life	Patient	Quality of life is a form of well-being measure, allowing triangulation with the WEMWBS
Social disability	Health of the Nation Outcome Scale	Researcher	To give opportunity to compare changes in well-being with social disability
Functioning	Global Assessment Functioning	Researcher	To give opportunity to compare changes in well-being with functioning

PPT, Positive Psychotherapy; PPTI, Positive Psychotherapy Inventory; WEMWBS, Warwick-Edinburgh Mental Well-Being Scale.

### Fidelity assessment

Corresponding with the strategies to improve treatment fidelity, we use fidelity measures at three of the five levels of fidelity, i.e., study design, provider training, and treatment delivery. The other two levels of fidelity – treatment receipt and skills enactment – will be assessed as part of the process evaluation.

To assess fidelity at the study design level, deviations from session lengths and the length of mid-week calls is recorded (to establish treatment dose) and group cancellations and any changes to group times are recorded (to identify implementation setbacks). To assess fidelity at the provider training level, facilitators’ presence at training and supervision sessions is recorded. To assess fidelity at the treatment delivery level, adherence to treatment protocol is rated by the co-facilitator for each session on a fidelity evaluation scale developed for WELLFOCUS PPT.

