**Methods/Design:**

This study is a non-blinded pragmatic pilot RCT comparing WELLFOCUS PPT provided as an 11-session group therapy in addition to treatment as usual to treatment as usual alone. Inclusion criteria are adults (aged 18–65 years) with a main diagnosis of psychosis who use mental health services. A target sample of 80 service users with psychosis are recruited from mental health services across the South London and Maudsley NHS Foundation Trust. Participants are randomised in blocks to the intervention and control group. WELLFOCUS PPT is provided to groups by specifically trained and supervised local therapists and members of the research team. Assessments are conducted before randomisation and after the group intervention. The primary outcome measure is well-being assessed by the Warwick-Edinburgh Mental Well-being Scale. Secondary outcomes include good feelings, symptom relief, connectedness, hope, self-worth, empowerment, and meaning. Process evaluation using data collected during the group intervention, post-intervention individual interviews and focus groups with participants, and interviews with trial therapists will complement quantitative outcome data.

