#### Objective 3: Piloting the evaluation strategy

To test approaches to assessing fidelity, process evaluation, and outcome evaluation, to inform the design of a future definitive RCT including choice of primary and secondary outcome measures, and sample size calculation.

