### Process evaluation

The aim of the process evaluation is to test the intermediate processes outlined in the WELLFOCUS model between the intervention (tested by fidelity assessment) and outcome. Process evaluation strategies include ratings and notes taken by the co-facilitators directly after each session and phone call for each participant and each week, and additional qualitative interviews and focus groups after the end of the therapy.

The co-facilitator collected process evaluation includes five assessment strategies at treatment receipt and skills enactment level which map onto the WELLFOCUS intervention model:

1. Presence of participants in group sessions

2. Engagement of participants in exercises during treatment groups and a facilitator rating of whether this was perceived as beneficial

3. Facilitator rating of behavioural intent to undertake the ‘ongoing exercise’, based on the session in which the ‘ongoing exercise’ was set

4. Facilitator rating of engagement and benefit from the ‘ongoing exercise’, based on the session in which the ‘ongoing exercise’ was reviewed

5. Length and content of the weekly telephone calls.

Qualitative process evaluation comprises individual interviews and focus groups with trial participants, and individual interviews with group facilitators. Participants will be asked to take part in either an individual interview (50%) or a focus group (50%).

Semi-structured interviews will ask about participants’ experience of taking part in the study, how the intervention was delivered, and what impact the intervention has had on their well-being and life generally. Questions will also relate to the WELLFOCUS model and processes facilitated by the therapy. Suggestions for further improving the intervention and trial processes will be collected. As far as possible, those who dropped out of the intervention arm or attended irregularly will be asked for reasons including contextual factors influencing attendance and for suggestions to improve attendance rates in the definitive RCT. Focus groups will also allow discussion of any suggestions for improvements of the intervention. Hence, topics that come up in interviews, particularly about problematic issues in relation to therapy content, delivery, and study procedures, will feed into focus groups.

All clinicians involved in providing the therapy will be interviewed to obtain feedback on the WELLFOCUS manual, the intervention delivery, and the trial procedures.

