### Assessment

Outcomes are measured pre-randomisation and at the end of the intervention (i.e., 3 months after baseline). Every effort will be made to include patients who drop out of treatment in the follow-up assessments to enable intention-to-treat analysis [30]. Process and fidelity measures are collected by the co-facilitators for each participant after each group session. Qualitative process evaluation is conducted with those in the intervention arm, who are asked to participate either in an individual interview or in a focus group (with alternating allocation based on finishing order of groups). Participants are offered £20 as compensation for their time after completing each assessment and either the interview or focus group (i.e., £60 in total for intervention, £40 for control). The £20 difference in payment between the groups might increase follow-up rates for the process evaluation data from intervention group participants, but remuneration for the outcome evaluation is the same for both groups.

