#### Addressing bias in the intervention

Fidelity to the WELLFOCUS manual is monitored to ensure comparability of the intervention between local groups.

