#### Objective 3: Piloting the evaluation strategy

The usefulness of fidelity and process evaluation approaches will be determined by exploring whether researcher ratings of fidelity to the manual and process factors, such as engagement and beneficial effect of exercises, helps to improve prediction of outcome and future attendance as compared to recording group attendance only. The confidence interval approach will be used to help determine the suitability of the outcome measures and to inform the sample size calculation for a definitive RCT. This approach involves estimating the confidence interval of the difference between intervention and control group at follow-up, adjusted for baseline. The inclusion of zero (i.e., point of no effect) and the inclusion of a clinically relevant effect into the confidence interval will help to estimate the suitability of measures for a definitive RCT [28]. Further considerations to be taken into account for the choice of outcome measure for the definitive RCT will include the acceptability of the scale (as measured by the number of missing responses), the magnitude of correlation between baseline and follow-up on this scale, and the overall variance of the scale. The group means, standard deviations, and correlations between baseline and follow-up will be used to inform the sample size calculation for the definitive RCT.

In addition, outcomes will be analysed to estimate effectiveness of the intervention. This analysis will be done on an intention-to-treat basis, with participants analysed in the group to which they were randomised irrespective of their compliance with the assigned trial arm. To estimate effectiveness of the intervention, WEMWBS (primary outcome) at pre-treatment (baseline) and 3-month follow-up will be analysed using a random effects regression of outcome on trial arm adjusted for baseline score including a random effect to allow for between group variations in the intervention arm. Where relevant, we will also consider using other approaches to address missing data such as complier-average causal effect approaches [63].

Divergence of normality will be assessed for the distribution of all variables as will linearity of correlations and equality of variance. The choice of statistical methods will be adapted accordingly. *P* values of 0.05 will be considered significant in all cases. All analyses will be carried out in SPSS Version 20 and Stata Version 12.

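### Adherence to the manual is rated once per session, by a co-facilitator who helped deliver it, on a newly built scale, so the pilot cannot estimate inter-rater agreement for a measure it sets out to test

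*Protocol article*

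**What the plan says.** Intervention group section: "WELLFOCUS PPT is provided by two facilitators who follow the WELLFOCUS PPT manual". The abstract adds that the therapy is "provided to groups by specifically trained and supervised local therapists and members of the research team".

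Fidelity assessment section: "adherence to treatment protocol is rated by the co-facilitator for each session on a fidelity evaluation scale developed for WELLFOCUS PPT". The scale is specific to this intervention, and the rater is named in the singular.

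Process evaluation section: the process data include "ratings and notes taken by the co-facilitators directly after each session and phone call for each participant and each week". Items 2 to 4 of the list there are judgement ratings of engagement, benefit and intent. The Assessment section repeats the source: "Process and fidelity measures are collected by the co-facilitators for each participant after each group session".

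The article puts these data to three uses:
- Objective 3 in the Aims is "To test approaches to assessing fidelity, process evaluation, and outcome evaluation".
- The Objective 3 analysis judges usefulness by "exploring whether researcher ratings of fidelity to the manual and process factors, such as engagement and beneficial effect of exercises" improves prediction of outcome and later attendance over attendance alone.
- The section on bias in the intervention states: "Fidelity to the WELLFOCUS manual is monitored to ensure comparability of the intervention between local groups".

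**The concern.** A definitive trial that takes over a new observer-type scale will want to know whether two people who see the same session score it alike. This pilot has two trained people in the room at every session but takes one adherence score, so it cannot answer.

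Two consequences follow. First, if the ratings fail to improve prediction, the pilot cannot tell an uninformative measure from an unreliable rating of a useful one, and the definitive trial could drop the measure for the wrong reason. Second, the comparability statement reads the ratings across groups. A lenient rater would look like better delivery in the groups or sessions that this person rated.

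The article protects other measurements from this problem. Post-treatment outcomes are, where possible, assessed by researchers outside the participant's group, and interviews and focus groups are, as far as possible, led by someone who did not deliver the intervention to those participants. The session ratings have no such protection.

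**Working it through.** The plan gives no figure for agreement, so there is none to reproduce.

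**Inputs.** Five waves, with about 8 intervention participants each (Sample size); 11 sessions (Intervention group); one adherence rating per session (Fidelity assessment).

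**Do other safeguards supply a second rating?**
- The 10% double rating under Data handling is aimed at transcription errors.
- The concordance training in the same section covers standardised assessments. The new scale is not named.
- The post-session notes by both facilitators are written jointly, so they are not two independent ratings.
- The facilitator pool is cover for absence, not a plan to cross raters over groups.

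None does.

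**Agreement as planned.** Sessions: 5 × 11 = 55. Degrees of freedom for rater disagreement: n(k − 1), with n sessions and k ratings per session. With k = 1 this is 55 × 0 = 0, so agreement is not estimable. With k = 2 it is 55 × 1 = 55.

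**Precision with paired ratings** (assumed observed ICC; sessions treated as independent). Fisher-z, with SE = 1/√53.5 = 0.137:
- ICC 0.80: z = 1.099 ± 0.268, giving 0.68 to 0.88.
- ICC 0.60: z = 0.693 ± 0.268, giving 0.40 to 0.74.

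F-based intervals for a one-way ICC with two ratings per session:

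| Sessions rated twice | ICC 0.5 | ICC 0.7 | ICC 0.8 |
|---|---|---|---|
| 55 | 0.27 to 0.67 | 0.54 to 0.81 | 0.68 to 0.88 |
| 28 | 0.17 to 0.73 | 0.45 to 0.85 | 0.62 to 0.90 |
| 11 | −0.08 to 0.83 | 0.23 to 0.91 | 0.44 to 0.94 |

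The 55 sessions are 11 repeats in each of five groups with few raters, so the first row is probably too narrow. The lower rows show what a subsample would give. They also indicate the width if clustering reduced the information to that of 28 or 11 independent sessions.

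**Prediction analysis.** A score with reliability ρ shrinks a true correlation by √ρ. With an assumed ρ = 0.5, √0.5 = 0.71. The mean of two ratings with independent errors has reliability 2 × 0.5/(1 + 0.5) = 0.67, and √0.67 = 0.82.

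**Group against rater.** Separate effects need a design matrix of rank (groups + raters − 1). The article does not say how co-facilitators are assigned, so these are cases, not facts:
- One rater per group: rank 5, needed 5 + 5 − 1 = 9. Fully aliased.
- Three raters covering whole groups: rank 5, needed 5 + 3 − 1 = 7. Only groups that share a rater can be compared.
- Four raters rotating by session: rank 8, needed 8. Separable.
- Paired ratings by five non-overlapping pairs: rank 10, needed 5 + 10 − 1 = 14. Disagreement within a pair is estimable, but the pair's common level is still aliased with group.

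If raters account for an assumed 10% to 30% of rating variance, each group has its own rater and the groups do not differ at all, the apparent between-group share is 0.10 to 0.30.

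**The case against.** Much can be said for the plan. Its own test of these ratings, added prediction over attendance, can be run without a second rater. Fidelity monitoring does not rest on this scale alone: session and call lengths, cancellations, changed times and attendance at training and supervision are recorded too. Process data also include a participant-completed form and qualitative interviews. The inputs to the future sample size calculation are untouched. All of this stands, and it limits the weight of the point. It does not supply an agreement estimate.

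Several stronger readings are tempting but not supported:
- *Each group has one rater, so group and rater are wholly confounded.* Assignment is not stated, and cover from the pool could create some overlap. Confounding is a risk, not an established fact.
- *The same person makes the fidelity and process ratings.* The article speaks of co-facilitators in the plural for the process data and does not say this.
- *No reliability can be estimated.* Only inter-rater agreement is lost. Internal consistency could be computed if the scale has several items.
- *The comparison of adherence across therapy groups under Objective 1 uses this scale.* It concerns participants' attendance, completion and homework, not facilitators' adherence to the manual.
- *The term researcher ratings in the Objective 3 analysis implies an outside rater.* It fits the Fidelity assessment section only where the co-facilitator belongs to the research team, and even then the rater took part in delivery.

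**Conclusion.** The point holds in limited form, as a cheap improvement and not a flaw in the trial's main analysis. The article fixes a single adherence rating per session, made by a co-deliverer on a newly developed scale, and describes no paired rating. Degrees of freedom for inter-rater disagreement are 0 over about 55 sessions, although the fidelity approach is itself under test. The prediction analysis can be run, but a null result would be ambiguous. The comparability claim can absorb rater differences to an extent that depends on how facilitators are assigned, which is not stated.

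The count assumes the planned five groups of 11 sessions. The intervals assume independent sessions and illustrative ICCs; the attenuation factors assume a reliability of 0.5.

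**What to change.** In the Fidelity assessment section:
1. Have both facilitators complete the fidelity scale independently after each session, before the joint notes, and record the rater's ID.
2. Do the same for the engagement, intent and benefit ratings (items 2 to 4 under Process evaluation), in a subsample of sessions if the load is too great.
3. Report agreement (ICC or weighted kappa) with an interval that allows for clustering of sessions within the five groups.
4. Use the mean of the two ratings in the Objective 3 prediction analysis.
5. State that these are deliverers' own ratings, and that shared optimism and confounding of group with facilitator pair remain unless facilitators overlap across groups. Limit the comparability statement accordingly.
6. Reconcile the rater named in the Fidelity assessment section with the researcher ratings named in the Objective 3 analysis.

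Cost: a few minutes of the second facilitator's time at each of about 55 sessions, with no extra staff. Full duplication of the participant-level ratings would cost more, up to about 8 × 11 × 5 = 440 participant-sessions, hence the subsample option. Agreement between two co-deliverers may also overstate what an outside rater would find.
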